### Data collection methods and management

2.13

Study data will be collected using standardized electronic case report forms and stored in a secure, pseudonymized database. Identifying information will be stored separately from research data. Direct identifiers, such as name and contact information, will only be accessible to authorized healthcare professionals at the recruiting site, or to authorized coordinating personnel when strictly required for study management or participant safety. The coordination team will routinely access pseudonymized study data only.

Data will be hosted on an encrypted Google Cloud Platform server using Cloud Firestore, a scalable NoSQL database, in the Europe-west region (Zurich, Switzerland). Access to the platform and database will be role-based, password-protected, and restricted to the minimum information required for each user profile. Any data correction after verification will require an authorized and documented amendment, with an audit trail maintained within the system.

Data handling, storage, and protection procedures will comply with Regulation (EU) 2016/679, the General Data Protection Regulation, and Spanish Organic Law 3/2018 on Personal Data Protection and guarantee of digital rights.

### Data monitoring

2.14

Data and safety monitoring will be performed by the principal investigator and coordinating center throughout the trial. Monitoring will include remote review of recruitment and follow-up status, informed consent documentation, data completeness and consistency, adverse event records, app-recorded safety information, and adherence to intervention and assessment procedures. Deviations or data-quality issues will trigger documented corrective actions. The Diactive-1 web portal will provide a timestamped audit trail of relevant user actions, enabling remote verification of data integrity and site compliance. No formal data monitoring committee will be established, as the intervention is low-risk, non-pharmacological, and conducted alongside standard clinical care. Safety monitoring will remain independent of the funder, and any potential conflicts of interest will be disclosed in the “Funding” and “Conflicts of Interest” sections.

No interim efficacy analyses or formal stopping rules have been planned. However, if safety concerns, recurrent serious adverse events, or protocol-related risks are identified, the principal investigator may recommend temporary suspension, protocol amendment, or early termination of the trial. Any such decision will be documented and reported to the relevant ethics committee and institutional bodies in accordance with applicable regulations and local procedures.

### Statistical analysis

2.15

The R version and packages used will be reported. Cross-sectional analyses with baseline data will follow the STROBE statement, while the final reporting of the RCT will adhere to CONSORT 2025 (62). A two-sided α level of 0.05 will be used to determine statistical significance for the primary outcome.

Normality, descriptive statistics and group differences: Distributional properties of continuous variables will be evaluated through graphical inspection (i.e., histograms and Q–Q plots) and formally assessed using the Shapiro–Wilk test when appropriate. Homogeneity of variance will be examined using Levene’s test. Continuous variables will be summarized as mean ± standard deviation (SD) when approximately normally distributed, or as median and interquartile range (IQR) otherwise. Categorical variables will be presented as absolute and relative frequencies. Baseline characteristics will be summarized by randomized group using descriptive statistics, without formal hypothesis testing. Any baseline differences will be interpreted descriptively and clinically.

Missing data: Missing data will be examined using graphical and tabular summaries by variable, treatment group, and time point. The number and percentage of missing observations and missingness patterns will be reported separately by randomized group. Compatibility with a missing completely at random (MCAR) mechanism will be assessed using Little’s MCAR test, together with comparisons of baseline characteristics between participants with and without missing outcome data as a supplementary analysis. A missing-at-random (MAR) mechanism will be explored by modeling missingness indicators as a function of observed variables. A missing-not-at-random (MNAR) mechanism will be considered when missingness remains plausibly related to unobserved values or post-randomization events not fully explained by observed data.

The primary intention-to-treat (ITT) analysis will use all available outcome data through maximum-likelihood estimation in the prespecified linear mixed-effects model under a MAR assumption. This likelihood-based approach does not require explicit imputation of missing outcomes and is appropriate for longitudinal continuous outcomes when at least MAR is considered plausible (63). Multiple-imputation sensitivity analyses will be conducted if the primary outcome at 12 weeks is missing for at least 5% of the participants randomized to either treatment group (64). Multiple imputation will also be performed if the reasons for missingness raise concerns about the plausibility of the MCAR or MAR assumption. Then, multiple imputations will be performed using chained equations within each randomized group (65), including baseline and post-intervention measurements, hospital, and potential variables associated with missing data for the primary outcome.

Cross-sectional analysis: Associations between categorical variables will be examined using Pearson’s chi-square test or Fisher’s exact test, as appropriate. For quantitative variables, associations will be assessed using Pearson’s correlation coefficient or Spearman’s rho (ρ), depending on distributional assumptions and the linearity of the association. Between-group comparisons, when relevant for cross-sectional exploratory analyses, will be performed using independent-samples t tests or one-way analysis of variance for approximately normally distributed variables, and Mann–Whitney U or Kruskal–Wallis tests for non-normally distributed variables. Regression analyses will be performed using the modeling framework most appropriate to the scale and distribution of the outcome, the functional form of the association, and the data structure. Model selection will therefore consider normality, homoscedasticity, linearity, and clustering or nesting when applicable.

Effect of the intervention: The intervention effect will be estimated for the primary outcome using linear mixed-effects models under the ITT principle, with participants analyzed according to randomized allocation. Baseline and 12-week outcome values will be jointly modeled as repeated outcome measurements using data in long format. Models will include fixed effects for group, time, and the group × time interaction, with random intercepts for hospital and participant nested within hospital. Because baseline outcome values are included as repeated measurements, they will not be entered as separate covariates. The primary treatment effect will be estimated from the group × time interaction, representing the between-group difference in change from baseline to 12 weeks (i.e., over time). The same modeling framework will be applied to the prespecified secondary continuous outcomes, with correction for multiple testing within outcome families using the Benjamini–Hochberg false discovery rate procedure (66).

The primary model for handgrip strength will include no additional covariates. Prespecified adjusted models for glycemic outcomes will additionally include baseline daily insulin dose and baseline carbohydrate intake, whereas models for daily insulin dose will include baseline carbohydrate intake. These covariates were selected *a priori* because of their established prognostic relationships with the corresponding outcomes. No other covariates will be included in these prespecified models (67). Any additional unplanned adjusted analyses will be clearly identified as *post hoc* sensitivity analyses and will not be selected solely on the basis of observed baseline differences between groups (62).

In addition to the primary ITT analysis, per-protocol (PP) analyses will be conducted including intervention participants who complete an average of at least two resistance-training sessions per week during the 12-week intervention (68), provided that these sessions are reasonably distributed across the intervention period rather than concentrated in a limited number of weeks, and usual-care participants with available primary outcome data and no major protocol deviations.

Unstandardized coefficients with 95% confidence intervals (CIs) will be used to estimate marginal means and group contrasts over time, which will be reported as mean differences (MDs). Standardized effect sizes, including Cohen’s d when appropriate, will be reported as complementary measures (69). For categorical outcomes, between-group effects will be estimated using risk differences (RDs) and relative risks (RRs), with 95% confidence intervals. When clinically interpretable, the number needed to treat, or harm, will be calculated from absolute risk differences. Effect sizes for differences in proportions will be estimated using Cohen’s *h*.

Model diagnostics will be examined to assess distributional assumptions, heteroscedasticity, and influential observations. If substantial departures are detected, robust linear mixed-effects models preserving the same fixed- and random-effects structure as the primary models will be considered. Sensitivity analyses may include restricted longitudinal data analysis under a common-baseline assumption of baseline variables showing clinically relevant imbalance between groups (70). Effect modification by sex, pubertal status, insulin delivery modality, insulin type, and CGM system will be explored by adding interaction terms to the primary model. These analyses will be considered exploratory.

Other exploratory analyses: Exploratory analyses will examine whether the magnitude of the intervention effect varies according to intervention exposure, adherence, and training-related characteristics. Dose–response analyses will use app-derived indicators of intervention exposure, including training frequency, completion of prescribed sessions, accumulated training volume, session duration, active and recovery times, training time, training type, and, when available, heart-rate metrics or perceived exertion. We will also explore whether within-participant changes in the primary and secondary outcomes are associated with changes in other clinical, behavioral, and physical-fitness variables. These change–change associations will be examined using regression models adjusted for treatment group, baseline values, hospital, and other relevant prespecified covariates. All such analyses will be considered exploratory and will not be interpreted as providing evidence of causal relationships.

Moreover, participants will be classified as responders or non-responders according to prespecified thresholds based on clinical guidelines (38), or minimally relevant standardized effect sizes (71), with the direction of beneficial response defined separately for each outcome. Response prevalence will be calculated by treatment group and compared using the χ² test. Additional longitudinal models may include responder status interaction to explore whether intervention effects differ between responder categories. To identify baseline profiles associated with response, exploratory regression models will be fitted. These analyses will be considered hypothesis-generating.

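### Doubt about missing-at-random is answered with an imputation that still assumes it, so the MNAR case the protocol raises has no analysis

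*Protocol article*

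**What the plan says.** All of this is in the protocol article, section 2.15 (Statistical analysis), in the text on missing data.

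- The primary intention-to-treat analysis uses "maximum-likelihood estimation in the prespecified linear mixed-effects model under a MAR assumption".
- Multiple imputation has two triggers. The first is at least 5% of week-12 primary outcomes missing in either arm. The second is a matter of judgement: "Multiple imputation will also be performed if the reasons for missingness raise concerns about the plausibility of the MCAR or MAR assumption".
- Both triggers lead to one procedure: "multiple imputations will be performed using chained equations within each randomized group (65), including baseline and post-intervention measurements", with the further inputs "hospital, and potential variables associated with missing data for the primary outcome".
- On missing not at random (MNAR), the section says: "A missing-not-at-random (MNAR) mechanism will be considered when missingness remains plausibly related to unobserved values or post-randomization events". No analysis follows from that sentence.

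The remaining analyses in section 2.15 are robust mixed models, a common-baseline longitudinal model prompted by baseline imbalance, and a per-protocol analysis. None of them relaxes MAR for missing week-12 values.

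**The concern.** A sensitivity analysis for missing data is useful when it varies the assumption in doubt. Here the second trigger fires when MAR itself looks implausible, and the response is an imputation that, as described, needs MAR to be valid. No delta shift, reference-based step, pattern-mixture model or tipping point is stated.

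This matters because participants and clinicians are unblinded (section 2.5), the training is done at home, and 15% attrition is planned (section 2.4). Young people who gained little may plausibly be the ones who miss the week-12 visit. If that dependence remains after conditioning on observed data, likelihood and imputation estimates can be wrong together. Their agreement could then be reported as robustness although the doubtful assumption was never changed.

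**Working it through.** **1. Inputs and the plan's own figures (section 2.4).** Effect 0.24 z, d = 0.56, two-sided α = 0.05, 67 evaluable per arm, 15% attrition, 79 randomised per arm.

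- Implied SD = 0.24 / 0.56 = 0.4286.
- Power by noncentral t with 132 df is 89.6%, as stated.
- 134 / 0.85 = 157.6, rounded up to 158, as stated.

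**2. Does doubt about MAR lead to a different analysis?** The 5% trigger needs 0.05 × 79 = 3.95, so 4 missing in one arm. Planned attrition implies 0.15 × 79 = 11.85, about 12 per arm. Imputation would therefore probably run on the first trigger, and the second adds nothing to it.

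**3. What each analysis conditions on.**

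- Primary model: arm, time, hospital and baseline handgrip, with no further covariates.
- Imputation: the same information plus observed predictors of missingness.
- Neither allows missingness to depend on the week-12 value once these are given.

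**4. Simulation.** 1,500 trials of 79 against 79, true effect 0.24, about 15% missing per arm, 20 imputations. These settings are assumptions that are not in the protocol: baseline SD 1; change SD 0.43; an auxiliary variable correlated 0.6 with change; in the two non-MCAR scenarios, intervention-arm dropout with a log-odds slope of −1.5 per SD and control dropout completely at random. Mean estimates (Monte Carlo SE about 0.002):

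| Missingness | ML mixed model | MI, baseline only | MI with auxiliary |
|---|---|---|---|
| MCAR | 0.238 | 0.239 | 0.240 |
| Driven by the observed auxiliary | 0.286 | 0.285 | 0.240 |
| Driven by the unobserved change (MNAR) | 0.318 | 0.319 | 0.294 |

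In the second row, imputation with the right auxiliary removes the bias. In the third, ML and baseline-only imputation agree to 0.001 while both are about 0.08 too high (0.078 / 0.24, one third). A good auxiliary still leaves 0.294 − 0.24 = 0.054.

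**5. What an MNAR analysis would show.** Let p be the missing fraction in an arm and δ the mean departure of its missing values from what MAR predicts. Then

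effect = 0.24 + p_I δ_I − p_C δ_C.

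With p_I = 0.15 and δ_C = 0:

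- δ_I = −0.24 (dropouts gain nothing over usual care): 0.24 − 0.036 = 0.204.
- δ_I = −0.43: 0.24 − 0.065 = 0.175.
- δ_I = −0.86: 0.24 − 0.129 = 0.111.

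Tipping point at planning values, with the SE held fixed:

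- SE = 0.4286 × √(2/67) = 0.0740.
- Lower 95% limit = 0.24 − 1.978 × 0.0740 = 0.094.
- Required departure = 0.0935 / 0.15 = 0.62 z.

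Equal missing fractions with equal departures cancel in the formula, so both arms need to be varied.

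**The case against.** The strongest reply is that the imputation is more than a repeat of the primary model. That model has no added covariates, whereas the imputation brings in observed predictors of missingness and so rests on a weaker form of MAR. App-recorded sessions (sections 2.8.4 and 2.10.17) show who stopped training in the intervention arm. The wording permits their use, and imputing within arm accommodates predictors that exist in one arm only. The trigger also names MCAR, for which imputation is a sound response. All of this stands. A reader might infer that the imputation can detect nothing and must reproduce the primary result; the text does not support that, and the second row of the table contradicts it.

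A reader might also infer that dropouts are given the gains of programme completers. That is not what is described. The imputation draws on everyone in the arm with a week-12 value, including poor adherers who attend, and it conditions on their observed data. Section 2.12 says that stopping exercise for the listed safety or medical reasons does not automatically end follow-up.

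A third reply is that MNAR detail belongs in a statistical analysis plan that is not shown. This is fair for delta values or a reference profile. It does not cover the rule the article does state, which sends doubt about MAR to a MAR method.

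Finally, the tipping point is far out: 0.62 z is about 1.45 times the implied SD and 2.6 times the planned effect. That also stands. At planned attrition, the size of the estimate is more exposed than its significance.

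**Conclusion.** The point holds in a limited form. The stated response to doubt about MAR remains a MAR analysis, conditional on more observed data. It is adequate for doubt about MCAR and where observed predictors account for the missingness. It leaves unanswered the case the section itself raises, missingness that still depends on unobserved values. The primary analysis stands; what would be untested is a claim that it is robust to MNAR.

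The sizes are illustrations. The 0.204 assumes that every intervention dropout gains nothing over usual care and that 0.24 is the effect in those observed. Section 2.4 gives 0.24 only as the between-group difference in the previous trial, so a reader should not conclude that the planned effect is overstated by a known amount. The simulated bias of about 0.08 depends on the assumed dropout mechanism. The near-identity of likelihood and imputation on the same variables does not depend on that mechanism; it follows from the MAR assumption they share.

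**What to change.** In section 2.15, or in the statistical analysis plan:

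- Describe the chained-equation imputation as a MAR sensitivity analysis with auxiliary variables, and name app-recorded participation among the candidate predictors in the intervention arm.
- For the trigger concerning doubt about MAR, or under the existing 5% trigger, specify an MNAR sensitivity analysis of the week-12 handgrip z-score. A delta-adjusted imputation with a tipping point, with delta varied separately in both arms, would serve. Reference-based imputation of the intervention arm from the usual-care profile may be added.
- Attach that analysis to the sentence saying that MNAR will be considered, and fix the range of deltas before the analyst is unblinded.

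Running these analyses whenever a single outcome is missing would go further than the defect requires. The cost is a change of wording and a few hours of analysis. The downside is a sensitivity estimate that may be less favourable than the primary one.

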In the 2026 Standards of Care in Diabetes, the American Diabetes Association (ADA) continues to recommend ≥60 minutes per day of moderate-to-vigorous physical activity and ≥3 days per week of muscle-strengthening activities for children and adolescents, recognizing exercise for the first time as an effective therapeutic strategy (20). However, a key challenge lies in enabling youth with type 1 diabetes to translate guideline-based recommendations into daily practice while understanding their individual glycemic responses to exercise. To address this gap, Diactive-1 was developed as an mHealth tool that leverages the widespread use of smartphones worldwide (21) to deliver tailored resistance training programs, responding to the limited evidence on the isolated effects of this modality (22), while incorporating glycemic monitoring around exercise to provide evidence-based recommendations (18). Our previous randomized clinical trial (RCT) conducted in Navarre, Spain, involving 62 youth with type 1 diabetes showed high usability of Diactive-1, with a score of 4.33 out of 5.00 (23), and demonstrated that participants allocated to the intervention group maintained glycemic stability while achieving significant reductions in daily insulin dose at 12 and 24 weeks compared with usual clinical care, with no reported hypoglycemic events (10). These benefits were accompanied by improvements in muscular strength, lean mass, and bone mineral content (24). Thus, Diactive-1 may have potential as an adjunctive tool to standard treatment by empowering youth to optimize daily type 1 diabetes management. However, the initial RCT was conducted in a single clinical context with a limited sample size, and the effectiveness of Diactive-1 across other hospital settings and clinical workflows remains uncertain. This could be addressed by scaling up Diactive-1 across multiple hospitals, incorporating an updated algorithm, refining the training program, and enhancing usability to promote greater engagement. Therefore, the primary aim of this multicenter randomized controlled trial is to evaluate the effectiveness of Diactive-1 (v2.0) in improving handgrip strength in children and adolescents with type 1 diabetes. Secondary aims are to examine its effects on glycemic stability, insulin requirements, cardiometabolic markers, physical literacy, quality of life, psychological well-being, and app-related engagement outcomes.

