### Sample size and recruitment

2.4

Based on preliminary 12-week intervention data from the previous Diactive-1 trial, the between-group difference in handgrip strength z-score was 0.24 units, corresponding to an approximate standardized effect size of Cohen’s d = 0.56 (10). Using G*Power for an independent-samples comparison with a two-sided α = 0.05, 134 evaluable participants (67 per group) would provide 89.6% power, rounded to approximately 90% (27). After allowing for an anticipated attrition rate of 15%, the recruitment target was set at 158 children and adolescents in total, with 79 participants allocated to the intervention group and 79 to the usual-care group (28). Sampling will be extended until the end of the recruitment period, incorporating as many participants as possible.

Because participants will be individually randomized within hospitals, this is not a cluster-randomized trial. Nevertheless, hospital-level effects will be accounted for in the planned mixed-effects analyses by including hospital as a random effect. As the actual hospital-level ICC is not yet known, a conservative *a priori* sensitivity analysis was conducted using the design effect DE = 1+(m−1)×ICC. Assuming a mean hospital size of approximately 14.5 participants and 15% attrition, ICC values of 0.01, 0.02, and 0.05 corresponded to effective sample sizes of approximately 120, 107, and 81 participants, with estimated powers of approximately 86%, 82%, and 70%, respectively. Thus, the planned recruitment is expected to retain more than 80% power under hospital-level ICC values of up to 0.02, whereas greater clustering would result in reduced power. Recruitment may continue beyond the target sample until the end of the prespecified recruitment period.

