### Secondary outcomes

2.10

Secondary outcomes assessed in Diactive-1 are summarized in **Table 1**. Secondary outcomes are organized hierarchically in: key secondary outcomes (i.e., glycemic-stability parameters and insulin requirements); descriptive or contextual outcomes (i.e., sociodemographic information, diabetes-related clinical characteristics, anthropometric parameters, pubertal maturation, intervention engagement, and barriers to physical activity); and exploratory or hypothesis-generating outcomes, including cardiovascular biomarkers and lipid profile; lifestyle-related outcomes (i.e., 24-hour movement behaviors and adherence to the Mediterranean diet); physical-domain outcomes (i.e., self-reported physical fitness and physical literacy); mental and psychosocial outcomes (i.e., psychological assessments, health-related quality of life, and screening for eating disorders); and implementation-related outcomes intended to explore usability, acute glycemic responses, and potential dose-response relationships (i.e., app usability and data recorded by the Diactive-1 app).

**Table 1 T1:** Summary of the variables examined in the randomized clinical trial.

Primary outcome	Measurement	Tool
Handgrip strength	Directly: Objectively	- Takei III Smedley Type 297 digital dynamometer. - Age- and sex-standardized z-score calculated using FitBack^©^ reference values.
Secondary Outcome	Measurement	Tool
Glycemic stability	Indirectly: - Objectively	- CGM downloads. (without brand distinction)
Insulin requirements	Indirectly: - Objectively - Self-reported	- Insulin pump downloads. - Smart-pen logs. - Insulin records from participants using CGM. (without brand distinction)
Cardiovascular biomarkers and lipid profile	Directly: - Objectively	- Laboratory testing at each hospital’s central laboratory. (standardized protocols)
Anthropometric parameters	Directly: - Objectively	- Height: SECA 213 stadiometer. - Weight: SECA electronic scale.
Maturity status	Indirectly: - Objectively	- Peak height velocity: Moore’s equation. - Tanner scale.
Self-reported fitness	Subjectively: - Self-reported	- International Fitness Scale (IFIS)
Physical literacy	Subjectively: - Self-reported	- Spanish Perceived Physical Literacy Instrument (S-PPLI)

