#### Glycemic stability

2.10.1

Glycemic parameters, including CGM wear time, mean glucose, glucose management indicator (GMI), time well above range (%TwAR; >250 mg/dL [>13.9 mmol/L]), time above range (%TAR; 180–250 mg/dL [10.1–13.9 mmol/L]), time in range (%TIR; 70–180 mg/dL [3.9–10.0 mmol/L]), time below range (%TBR; 54–70 mg/dL [3.0–3.8 mmol/L]), time well below range (%TwBR; <54 mg/dL [<3.0 mmol/L]), glycemic coefficient of variation (CV), hypoglycemic events (i.e., values <70 mg/dL [<3.9 mmol/L] lasting ≥15 min), and nocturnal hypoglycemic events (i.e., hypoglycemic events between 10:00 p.m. and 08:00 a.m.), will be obtained from CGM software regardless of the brand used.

Data will be collected during continuous 14-day monitoring periods before the baseline and 12-week medical visits (36). For descriptive and exploratory purposes, CGM data will also be collected during the 7 days after each visit, corresponding to the period in which carbohydrate intake and insulin-correction doses are prospectively recorded (37).

Glycemic targets will be evaluated according to ADA guidelines (38): HbA1c <7%, CV ≤36%, TwAR <5%, TAR <25%, TIR >70%, TBR <4%, and TwBR <1%. The glycemic risk index (GRI) score will be calculated as follows: (3.0 × TwBR) + (2.4 × TBR) + (1.6 × TwAR) + (0.8 × TAR) (39).

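### The CGM hypoglycemia measures fall under the Benjamini–Hochberg correction used for efficacy outcomes, which makes a real increase in hypoglycemia harder to flag, and the plan does not say how a harm result is judged

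*Protocol article*

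**What the plan says.** Section 2.10 (Secondary outcomes) names as "key secondary outcomes (i.e., glycemic-stability parameters and insulin requirements" and gives hypoglycemia no separate safety status. Section 2.10.1 (Glycemic stability) puts TBR, TwBR, hypoglycemic events and "nocturnal hypoglycemic events (i.e., hypoglycemic events between 10:00 p.m. and 08:00 a.m" in one list with mean glucose, GMI, time in range, the two above-range measures and the coefficient of variation, and it also defines the glycemic risk index (GRI).

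Section 2.15 (Statistical analysis) extends the primary mixed model, with its group × time test, to the prespecified secondary continuous outcomes, "with correction for multiple testing within outcome families using the Benjamini–Hochberg false discovery rate procedure". It does not list the families, give a false discovery rate level, or set a margin or harm-directed rule for hypoglycemia. The stated alpha is for the primary outcome only: "A two-sided α level of 0.05 will be used to determine statistical significance for the primary outcome". The same section plans group contrasts as mean differences with 95% CIs and does not describe those intervals as adjusted for multiplicity.

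Section 2.12 provides for adverse-event reporting in both arms and an app question about hypoglycemia after each session. Section 2.14 says: "No formal data monitoring committee will be established, as the intervention is low-risk".

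**The concern.** A multiplicity correction protects against false claims of benefit. For a harm measure the costlier error is the opposite one, failing to notice a real increase, and the correction makes that error more likely. The handicap also depends on something unrelated to safety: how many efficacy parameters share the family and how many of them show no effect.

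This matters because the Abstract and Introduction name fear of hypoglycemia as a main barrier to exercise in this population. The app's hypoglycemia question reaches app users only and has no control-arm counterpart. Other adverse events rely largely on reports in an unblinded trial. CGM is therefore the main objective comparison of hypoglycemia between arms, in a trial without a data monitoring committee.

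**Working it through.** **1. The plan's own figure.** Section 2.4 describes its calculation as "Using G*Power for an independent-samples comparison with a two-sided α = 0.05", with a difference "corresponding to an approximate standardized effect size of Cohen’s d = 0.56" and 67 per group. The noncentrality is d × √(n/2) = 0.56 × √33.5 = 3.24 on 132 degrees of freedom, which gives 89.6% power, as stated. Recruitment is 134 / 0.85 = 157.6, rounded up to 158. Both figures reproduce, so the same method is used below.

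**2. Inputs that the plan does not give (assumptions).**
- True increase in a hypoglycemia measure: 0.5 SD of the quantity compared, with 0.4 and 0.56 as alternatives.
- Family: the ten listed parameters other than wear time, plus GRI, so m = 11 (four hypoglycemia measures and seven others).
- False discovery rate level: 0.05.
- Two-sample t-tests on normal data, with no hospital effect.

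**3. One measure, no correction.** Noncentrality is 0.5 × √33.5 = 2.89 and the critical t is 1.98. The miss rate is 18% (power 82%). At 0.4 SD it is 37%, and at 0.56 SD it is 10%.

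**4. One measure, with Benjamini–Hochberg.** The i-th smallest p-value is compared with i × 0.05 / 11. The strictest threshold is 0.05 / 11 = 0.0045, and at that threshold the miss rate at 0.5 SD is 49.5%. The procedure relaxes as more tests succeed, so the remaining cases were simulated (67 per arm, 0.5 SD, m = 11):

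| What truly changes | Miss rate for one given hypoglycemia measure |
|---|---|
| One hypoglycemia measure only | 47–49% |
| All four hypoglycemia measures, the other seven null | 34–37% |
| All four, plus GRI and three others by 0.4 SD | about 28–29% |
| All four, plus all seven others by 0.5 SD | 21–23% |

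The first two rows cover correlations from 0 to 0.8 and the last two cover within-block correlations from 0.3 to 0.8. The third row deserves weight because Section 2.10.1 defines GRI as 3.0 × TwBR + 2.4 × TBR + 1.6 × TwAR + 0.8 × TAR, so GRI is unlikely to stay null when TBR and TwBR both rise.

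**5. Sensitivity to the assumed effect.** With the other measures null and m = 11 or 12, the single-measure miss rate is 59–71% at 0.4 SD and 20–35% at 0.56 SD.

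**6. Missing the increase altogether.** If all four measures rise by 0.5 SD and the others are null (m = 11 or 12), the chance that none of the four is flagged is 4–5% if they are independent, 16–17% at correlation 0.5 and 27% at correlation 0.8.

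**7. Interval against corrected test.** Suppose one measure shows an observed increase of 0.4 SD. Then t = 0.4 × √33.5 = 2.32 and p = 0.022. The unadjusted 95% CI is 0.4 ± 1.98 × √(2/67) = 0.4 ± 0.34, or about 0.06 to 0.74 SD, which excludes zero. Since 4 × 0.05 / 11 = 0.018 is below 0.022 and 5 × 0.05 / 11 = 0.023 is above it, the measure is flagged only if at least five of the 11 tests have p ≤ 0.023, or if a later step is met. Otherwise the interval shows an increase and the corrected test does not.

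**The case against.** The strongest reply is that the plan never says a non-significant corrected result will be taken as absence of harm. That is right. Section 2.15 commits to mean differences with 95% CIs, so much of what a safety reader needs is already planned. A reader might infer from "maintained glycemic stability while achieving significant reductions in daily insulin dose at 12 and 24 weeks compared with usual clinical care" in the Introduction that a null result will be reported as reassurance. That sentence summarises an earlier trial and continues with a separate statement about hypoglycemic events, so it does not show how this trial will be reported. Likewise, the low-risk description in Section 2.14 is the reason given for having no monitoring committee, not a conclusion to be drawn from the CGM test.

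Other routes also exist. Section 2.15 compares responder prevalence between arms by χ² using guideline thresholds, and Section 2.10.1 gives targets for TBR and TwBR. That comparison is labelled hypothesis-generating, but it is not said to be corrected. Adverse events are collected in both arms.

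Family membership is inferred, the event measures may be handled as counts, and listing families is commonly left to an analysis plan that is not shown. About 18 points of the miss rate at 0.5 SD come from sample size, and the Discussion already says that the trial is not powered for multiple secondary endpoints.

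All of this stands, and it limits the size of the point. It does not remove it: the document states a correction rule that covers harm measures, gives no exemption, and leaves open whether the interval or the corrected test decides.

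**Conclusion.** The point holds as a badly fixed analysis rule for a harm outcome. It does not affect the primary analysis. TBR and TwBR are covered by the stated correction; the two event measures are covered if analysed as continuous. On the inferred shared family, with 0.5 SD, 67 per arm and 11 tests, the chance of missing an increase in a given measure goes from 18% to roughly 28–49%. It falls to 21–23% only if every other parameter moves as well.

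A reader might infer that the plan misses a moderate rise in hypoglycemia about 36–50% of the time. The document does not support that as a property of the plan. Such a range needs an assumed effect, an assumed family and null results on all the efficacy measures, and it counts one named measure at a time. When all four rise, the chance that nothing is flagged is about 4–27%. A further inference, that a missed increase would be reported as no difference, is a risk left open by the wording and is not something the plan states.

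**What to change.** In Sections 2.10 and 2.15:
- Designate TBR, TwBR, hypoglycemic events and nocturnal hypoglycemic events as safety outcomes outside the Benjamini–Hochberg families.
- Report each between-arm difference with an unadjusted 95% CI.
- State that a non-significant p-value will not be taken as evidence of no increase, and that the interval governs any statement about harm.
- Keep the correction for any claim of benefit, including a claim that the app reduces hypoglycemia.

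This takes a few sentences and no new data. The cost is more false alarms. With four uncorrected two-sided 5% tests and no true difference, the chance of at least one nominally significant result is 1 − 0.95⁴ = 18.5% if they are independent (1 − 0.975⁴ = 9.6% in the harmful direction), and less if they are positively correlated. The report should say so.
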